## Abstract

**Background:**

Women with metastatic breast cancer (MBC) have average life expectancies of about 2 years, and report high levels of disease-related symptoms including pain, fatigue, sleep disturbance, psychological distress, and functional impairment. There is growing recognition of the limitations of medical approaches to managing such symptoms. Yoga is a mind-body discipline that has demonstrated a positive impact on psychological and functional health in early stage breast cancer patients and survivors, but has not been rigorously studied in advanced cancer samples.

**Methods:**

This randomized controlled trial examines the feasibility and initial efficacy of a Mindful Yoga program, compared with a social support condition that controls for attention, on measures of disease-related symptoms such as pain and fatigue. The study will be completed by December 2017. Sixty-five women with MBC age ≥ 18 are being identified and randomized with a 2:1 allocation to Mindful Yoga or a support group control intervention. The 120-min intervention sessions take place weekly for 8 weeks. The study is conducted at an urban tertiary care academic medical center located in Durham, North Carolina. The primary feasibility outcome is attendance at intervention sessions. Efficacy outcomes include pain, fatigue, sleep quality, psychological distress, mindfulness and functional capacity at post-intervention, 3-month follow-up, and 6-month follow-up.

**Discussion:**

In this article, we present the challenges of designing a randomized controlled trial with long-term follow-up among women with MBC. These challenges include ensuring adequate recruitment including of minorities, limiting and controlling for selection bias, tailoring of the yoga intervention to address special needs, and maximizing adherence and retention. This project will provide important information regarding yoga as an intervention for women with advanced cancer, including preliminary data on the psychological and functional effects of yoga for MBC patients. This investigation will also establish rigorous methods for future research into yoga as an intervention for this population.

**Trial registration:**

ClinicalTrials.gov identifer: NCT01927081, registered August 16, 2013

## Background

Although metastatic breast cancer (MBC) is a terminal illness, the development of more effective and better tolerated therapies has led to improved prognosis, with average life expectancies of 2 years or more. Nonetheless, women with MBC continue to report poor quality of life and high levels of pain and other disease-related symptoms including fatigue, sleep disturbance, psychological distress, and functional impairment [1]. Coping with these symptoms in the context of a life-limiting disease is very challenging [2, 3]. There is growing recognition of the limitations of medical approaches to managing cancer pain and related symptoms, and heightened interest in the role that self-management interventions can play in cancer symptom control [4]. Considering the challenging course of MBC along with the high prevalence of pain and associated symptoms and impairments, it is critical to develop effective interventions to enhance the quality of the remaining years of these women’s lives.

Recently there has been a growing interest in incorporating mind/body practices such as yoga and tai chi to help cancer patients cope with disease-related symptoms [5, 6]. The Office of Cancer Complementary and Alternative Medicine has prioritized studies of yoga and other mind/body therapies, as has the National Center for Complementary and Integrative Health [7, 8]. Yoga has been practiced in India for its proposed physical and mental benefits for thousands of years [9]. Yoga (which means ‘union’ in Sanskrit) aims at uniting mind and body through a variety of strategies such as practicing poses that promote strength, balance and flexibility [10–12]; breathing techniques that have soothing and energizing effects [13, 14]; and meditation to develop mental calm and emotional clarity [15].

Over the last several decades yoga interventions have been demonstrated to positively impact a variety of medical conditions, including hypertension [16, 17], asthma [18], multiple sclerosis [19], tuberculosis [20], back pain [21, 22], fibromyalgia [23, 24], and neck pain [25]. Yoga has also shown promise for improving cancer-related symptoms such as fatigue and stress [26]. However prior studies in cancer patients have been largely limited to early stage breast cancer patients and survivors. Thus far, five systematic reviews of randomized controlled trials (RCTs) of yoga for cancer have been published [27–31]. Three reviews included meta-analyses [27, 28, 30], and one of the remaining two focused exclusively on fatigue outcomes [31]. The number of RCTs included across the reviews ranged from 10 to 18, with sample sizes ranging from 18 to 164. Although the research quality across these studies varied greatly, on average the quality was relatively good (e.g., median quality = 67%, range 22–89% [27]). Most of the reviewed yoga interventions primarily emphasized physical poses, supplemented by some combination of breathing techniques, and relaxation or meditation practices. Approximately 50% of RCTs compared yoga with wait-list control conditions, and most of the remaining studies employed supportive care control conditions [29].

The consensus conclusion across the reviews was that there is moderate to good evidence that, at least in the short-term, yoga has a positive impact on psychological health in early stage breast cancer patients and survivors. Effect sizes for psychosocial outcomes (e.g., emotional distress, anxiety, depression, global quality of life) were moderate to large, whereas for functional well-being effect sizes were small. Fatigue improved in approximately 50% of studies where assessed. Only one RCT—which was conducted by the authors of this paper—assessed pain, which improved in that study [32]. None of the studies reported serious adverse events. Each of the available systematic reviews concluded that larger, more rigorous trials are needed and that these trials should include methodological improvements such as better control conditions, more physiological measures, longer term follow-up, and a wider range of cancer populations, including those with advanced cancer. A notable gap in the yoga for breast cancer literature is the absence of RCTs among individuals with advanced cancer. Recently, we conducted a pilot study to test a novel 8-week Mindful Yoga intervention designed to address the cancer-related pain, fatigue and emotional distress experienced by women with MBC. This intervention (previously published as ‘Yoga of Awareness’) showed promising results in terms of effects on these symptoms, and feasibility [33]. However, the MBC pilot study had major limitations including the lack of a control group, very small sample size (*N* = 13), and failure to address mediators that might explain the treatment effects.

In this paper, we present the design and detailed protocol of the first-known RCT of a yoga intervention for patients with advanced cancer. This single-blinded, randomized, attention-controlled, clinical trial for women with MBC has been funded by the National Center for Complementary and Integrative Health. Along with design considerations, we discuss the overall challenges of this trial as regards recruitment strategies, tailoring of the yoga intervention, and maximizing adherence and retention. We describe methods for addressing the theoretical and logistical issues encountered in conducting such a trial. Upon completion of the study, the results will be reported in accordance with the Consolidation of Standards for Reporting Trials (CONSORT) guidelines [34].

## Methods/Design

### Study Design

This is a randomized, controlled, single-blind, clinical trial of yoga in the treatment of cancer-related pain and associated symptoms in 65 women with metastatic breast cancer. Given the absence of prior yoga RCTs for patients with advanced cancer, our aims encompass the feasibility and acceptability of the Mindful Yoga intervention in this population, as well as comparing the efficacy of this intervention with a social support comparison condition. Feasibility will be indicated by our ability to meet accrual goals, and by at least 70% of patients attending ≥ 4 of 8 sessions and providing post-test assessments. Acceptability will be indicated by ≥ 80% of participants reporting satisfaction with the yoga intervention on a standardized measure of treatment effectiveness/satisfaction. Regarding efficacy, we hypothesize that the yoga intervention will lead to reductions in pain, fatigue, sleep disturbance, and psychological distress and increases in functional capacity compared to a social support intervention.

The social support comparison was chosen for several reasons. First, we sought to address literature reviewers’ criticism of the frequent employment of treatment-as-usual and wait-list control conditions in yoga for cancer RCTs [27–31]. Such comparisons fail to control for any factor other than the general passage of time. Second, based on our prior research and reviewer’s recommendations, we determined that the most important factors to control for were attention and time within a professionally-guided group intervention context. We ultimately decided on a social support comparison condition because previous studies indicate this type of intervention is viewed as highly credible by patients, and attendance at social support groups is comparable to that of other intervention groups [35–37]. Along with controlling for attention and time, this condition controls for nonspecific treatment effects such as general social support. The “single-blind” study design was chosen because it was not feasible to conceal assignment to the yoga intervention from participants and the intervention instructors. However, all study investigators and study staff involved in data collection will be masked to treatment condition, and statisticians will remain masked until the database is deemed final and ready for statistical analysis. As this is a low-risk behavioral trial, we do not foresee any circumstance under which blinded staff members will need to be unblinded during the trial.

Outcome assessments include intervention attendance rates, self-report measures of intervention satisfaction, pain, fatigue, sleep quality, psychological distress, mindfulness, a 6 min walk test measuring functional capacity, and treatment expectations. Assessments will be completed at baseline, post-treatment, and 3-month and 6-month follow-up. In addition, during the intervention period, participants will complete brief daily diaries on alternate weeks (4 weeks total) assessing symptoms (pain, fatigue, positive mood, negative mood, pain catastrophizing, pain acceptance) and yoga practice. An innovative feature of this study is that we will utilize these daily measures to conduct a rigorous test of two key psychological mediators that may explain the mechanisms of treatment effects. Pain theory and research point to two variables—pain catastrophizing (the tendency to focus on and exaggerate the threat value of painful stimuli and negatively evaluate one’s own ability to deal with pain) and pain acceptance (the willingness to experience pain and yet remain engaged in meaningful life activities despite pain)—that are likely to be particularly important in explaining the effects of the yoga intervention on pain and pain-related outcomes [38, 39]. Understanding the underlying mechanisms of the yoga intervention’s potential effects could have far-reaching implications for the design and evaluation of future yoga interventions for conditions entailing persistent pain.

The setting of the study is an urban tertiary care academic medical center located in Durham, North Carolina (Duke Cancer Institute). This study has been reviewed and approved by the Duke Medical Center Institutional Review Board (IRB). The study will adhere to the CONSORT guidelines for clinical trials [34]. The study flow is presented in Fig. 1.

**Fig. 1 Fig1:**
[figure not shown]
Study flow chart

### Study population

Participants in this study are women with age ≥ 18 who are receiving treatment for metastatic breast cancer (Stage IV breast cancer or recurrent metastatic breast cancer). Participants must have a life expectancy ≥ 9 months as estimated by their treating oncologist; speak and read English; and be able to understand study procedures and comply with them for the entire length of the study period. Individuals will be excluded if they have: (a) cognitive impairment as assessed by the 6-item Mini-Mental Status Exam; (b) Eastern Cooperative Oncology Group (ECOG) rating of ≥ 3 or Karnofsky Performance Status (KPS) < 60 as rated by the oncology provider; (c) too sick to participate, as determined by the treating oncologist; (d) received treatment for serious psychiatric illness (e.g., schizophrenia, severe depression) in the past 6 months; (e) current engagement in yoga practice ≥ 1 day per week; (f) resting systolic blood pressure > 180 mm and/or diastolic blood pressure > 100 mm, or resting heart rate > 100 beats per minute at the baseline assessment; (g) unable or unwilling to give written informed consent.

During the trial, all participants will continue to receive the usual care provided by their health care providers. Medications and treatments received during the study are documented and examined later in data analyses, but not restricted.

### Recruitment strategies

The percentage of MBC patients that accept entry when approached about behavioral intervention studies varies widely in the literature, from 27% [40] to 84% [41]. Our recruitment strategies focus on enrolling interested, completely informed participants, and we have projected a modest 25% acceptance rate for the present study. To address the significant gaps in research participation among minorities that limit the generalizability of findings, especially among African Americans (38% of the population in Durham County, North Carolina [42]), we are employing a variety of strategies to optimize minority participant involvement in the investigation.

Initial contact with potential participants is initiated by each patient’s health care provider, either verbally or by an IRB-approved introductory letter and pamphlet. Given the rapidly expanding interest in yoga among breast cancer patients [43], the introductory materials describe the yoga intervention as a “self-management discussion group + gentle exercise”, and the social support intervention as a “self-management discussion group”, with the aim of minimizing selection bias related to patients’ intervention preferences. This introduction includes graphics that are inclusive of various minority groups. Consistent with recommendations on the recruitment of African-American participants for clinical and prevention trials, particularly in oncology, we provide African-American (and all) potential participants with an opportunity to review the information about the study without any direct request to participate. Individuals who do not refuse further contact are called by a clinical research coordinator who has received training in how to address the social and cultural barriers to engaging African American cancer survivors in behavioral treatment studies. The study coordinator provides a brief scripted explanation of the study, answers any questions, and verifies eligibility. If the patient is eligible and chooses to participate, arrangements are made to obtain written consent and to administer the baseline assessment. As an added incentive, each participant is paid $190 for full participation in the study to offset costs participants might incur by participating (e.g., babysitters during sessions) and as an honorarium for their time.

### Adherence and retention strategies

Adherence and retention are crucial determinants of the quality and interpretability of clinical trials. Obstacles to treatment attendance when intervening with patients with advanced disease include a variety of illness-related issues, such as unpredictable worsening of symptoms, limited energy, and alternate patient priorities given shortened life expectancies. Strategies we have implemented to boost attendance are among the best practices used in many high quality behavioral intervention trials. These strategies include motivational interviewing during the recruitment phase, weekly reminder emails during the intervention phase, prompt calls from interventionists to participants who missed a class, and make up sessions. Adequate adherence in this trial has been defined as 70% of the participants attending full sessions (120 min each) for at least 4 of the 8 treatment sessions. This is a revision from the initial definition of adequate adherence, which specified 70% attendance of at least 7 intervention sessions. We believe that the revision represents a more reasonable expectation given the severity of illness in this patient population. In reviewing data from three previous studies of the 8-session Mindful Yoga intervention, it was apparent that the goal of 70% of participants attending at least 7 sessions was likely overly ambitious [32, 33, 44]. This was achieved in only one of the three previous studies, with a population of much healthier women who were post-treatment for early stage breast cancer [32].

Attrition is a recognized challenge in studying the MBC population, given the progressive nature of the disease. To minimize missing data, we developed a retention plan to ensure minimal dropout due to reasons other than death or severe disease progression. This plan has featured minimization of participant burden, provision of participant support through the intervention protocols, solicitation of information about participant difficulties and prompt response to concerns raised, and consistent efforts to optimize the participants’ experience of study participation. Continuous quality monitoring of retention key performance indicators has allowed us to rapidly identify and respond to problems.

### Sample size

Our original sample size of 60 patients (40 intervention and 20 control) was based mainly on the primary aim of intervention feasibility and acceptability. While we have increased the targeted enrollment to approximately 65 patients, statistical power to detect significant intervention differences remains limited. Nonetheless, our sample size will be sufficient to conduct longitudinal analyses of the outcome variables to inform the design of a larger-scale, multisite trial.

### Randomization

Participants are randomized with a 2:1 allocation to: (a) Mindful Yoga, or (b) a support group control intervention. The study statisticians ([name] & [name]) generated the randomization scheme prior to the start of recruitment, which is kept in a study database which is not accessible by blinded study personnel. The study coordinator who executes the randomization schedule does not have access to the data and is not involved in the outcome assessments.

Due to the group nature of the interventions, enrollment has proceeded in cohorts. Randomization has been stratified within each cohort using variable block sizes of 3 and 6. The study coordinator informs each participant of their assigned treatment condition following the baseline assessment and ≤ 14 days prior to the start of the interventions.

We planned to conduct cohorts of 20–25 participants, so that each intervention group (two yoga groups and one social support group per cohort) would have between 5 and 10 group members. After the first two cohorts, we found that class size was an important factor in the yoga classes, which functioned best with at least five patients in attendance, but that class size did not appear to impact the functionality of the social support classes. Given that attendance at each class is usually less than 100%, it is necessary to assign at least seven patients to each yoga class to meet the expectation of usually having at least five patients in attendance. This necessitates enrolling at least 20 patients per cohort to fill two yoga classes and one social support class.

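### The cohort minimum of 20 falls short of its own rule: at 2:1 allocation, two yoga classes of seven need 21 women on average and 22 for certainty

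*Protocol article*

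**What the plan says.** All the inputs stand in the Randomization section of the protocol article.

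- Allocation: "Participants are randomized with a 2:1 allocation to: (a) Mindful Yoga, or (b) a support group control intervention".
- Blocks: "Randomization has been stratified within each cohort using variable block sizes of 3 and 6".
- Groups: "two yoga groups and one social support group per cohort".
- Planned size: "We planned to conduct cohorts of 20–25 participants", with five to ten members in each group.

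After two cohorts the authors report that yoga classes worked best with five or more women present, and that size made no apparent difference to the support classes. Because some women miss any given class, they state that "it is necessary to assign at least seven patients to each yoga class", the purpose being "to meet the expectation of usually having at least five patients in attendance". From this they draw the cohort minimum: "This necessitates enrolling at least 20 patients per cohort to fill two yoga classes and one social support class".

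**The concern.** The minimum is presented as a consequence of the seven-per-class rule, but it does not follow from that rule and the allocation ratio. Two thirds of 20 is less than 14. In addition, 20 is not a multiple of 3, so a cohort of 20 always ends inside an unfinished block, and the number assigned to yoga is then a matter of chance.

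The minimum decides when a cohort may start, and it was set in response to a problem seen in the first two cohorts. Yet 20 was already the lower end of the planned range, so the remedy leaves the lower limit where it was. A cohort that starts at the minimum can, more often than not, break the rule that the minimum was meant to meet. What is at stake is the size of the yoga classes, and so how the intervention is delivered in a trial that tests whether it can be delivered.

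**Working it through.** **Inputs.** From the Randomization section: 2:1 allocation, two yoga classes per cohort, at least seven assigned to each, blocks of 3 and 6 within cohort, stated minimum 20. Assumptions: the 14 yoga women are split evenly between the two classes; the mix of block sizes is not given, so it is varied from all 3s to all 6s.

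**The stated figure.** A sum of 7 + 7 + 6 = 20 gives the article's number, but 14:6 is not 2:1. At 2:1, 20 women give 20 × 2/3 = 13.33 yoga places, or 6.67 per class. That is seven only after rounding up.

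**The minimum that follows from the rule.** Yoga places needed: 2 × 7 = 14. Women needed: 14 ÷ (2/3) = 21.

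**Shortfall at exactly 20.** The cohort can end in one of three positions:

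- Two into a block of 3, after 18 women and 12 yoga places. Both go to yoga with probability 1/3, so there are 13 places with probability 2/3 and 14 with probability 1/3.
- Two into a block of 6, after 18 women and 12 yoga places. The chances of 0, 1 or 2 more are 1/15, 8/15 and 6/15. Fewer than 14 has probability 9/15 = 0.60.
- Five into a block of 6, after 15 women and 10 yoga places. Three or four more follow with probability 2/3 and 1/3, so there are 13 places with probability 2/3.

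Every position gives 0.60 or 0.667, so any mix of block sizes lies between these values.

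**At 21.** Either the last block is complete, giving exactly 14, or the cohort ends three into a block of 6 after 12 yoga places. In that case only one more goes to yoga with probability 4/20 = 0.20. The shortfall risk therefore lies between 0 and 0.20.

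**At 22.** Either the cohort is one into a block after 14 yoga places, or four into a block of 6 after 12. A block of 6 holds only two support places, so at least two of those four go to yoga. The count is at least 14 in every case.

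| Cohort size | Mean yoga places | P(fewer than 14): all 3s | Equal mix | All 6s |
|---|---|---|---|---|
| 20 | 13.33 | 0.667 | 0.644 | 0.600 |
| 21 | 14.00 | 0 | 0.067 | 0.200 |
| 22 | 14.67 | 0 | 0 | 0 |
| 23 to 25 | 15.33 to 16.67 | 0 | 0 | 0 |

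With an equal mix, a cohort of 20 has 12 yoga places with probability 0.022, 13 with 0.622 and 14 with 0.356.

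**What one woman fewer means for a class (illustration).** The article gives no attendance rate, only that it is usually below 100%. If women attend independently, the chance of at least five present is:

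| Assumed attendance | Six assigned | Seven assigned |
|---|---|---|
| 65% | 0.32 | 0.53 |
| 70% | 0.42 | 0.65 |
| 75% | 0.53 | 0.76 |
| 80% | 0.66 | 0.85 |
| 90% | 0.89 | 0.97 |

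**The case against.** The strongest reply is that the gap is one woman, that the aim is only to have five present as a rule, and that 20 is a floor under cohorts planned at 20 to 25. Two sevens and a six do make 20, and support-class size is said not to matter. A class of six also lies within the planned five to ten members, and with 13 yoga women only one class is short, by one.

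Much of this stands: the gap is small, and the rule serves a soft target. It does not rescue the figure. The seven is stated as necessary, the 20 as what it necessitates, and a minimum cannot be rounded down and still meet its requirement. The 14:6 split arises in only 33 to 40% of cohorts of 20.

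Several stronger readings are tempting and are not supported:

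- A reader might infer that about two cohorts in three start with a short class. That rate holds only for cohorts of exactly 20, and the article gives no actual cohort sizes.
- A reader might infer that a class of six will usually have fewer than five present. On the illustration above that is so at 65 to 70% attendance and no longer so at 75% or more.
- A reader might infer harm to the primary attendance outcome. That outcome is counted per patient (at least 4 of 8 sessions), and nothing in the article links class size to a woman's own attendance.
- A reader might argue that three cohorts of 21 make 63, so enrolment stays within about 65. Two cohorts had already run, at sizes not given, so the number still to come cannot be derived.

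**Conclusion.** The point holds as an arithmetic inconsistency with a modest operational consequence. By the article's own inputs the minimum is 21 on average and 22 for certainty, not 20. At exactly 20 the shortfall probability is 0.60 to 0.67 for any mix of the two block sizes; at 21 it is at most 0.20; from 22 to 25 it is nil. These results assume that blocks start afresh in each cohort, as stratification by cohort implies, and that the last block may be left unfinished. The attendance figures are illustrations and the conclusion does not rest on them. The effect is on class size and intervention delivery; no effect on the primary outcome, the analysis or total enrolment is shown.

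**What to change.** For the remaining cohorts, change the minimum in the Randomization section from 20 to 22. Under the existing blocks this gives 14 to 16 yoga places, so seven or eight per class, and 6 to 8 in the support group, all within the planned five to ten. The randomization scheme stays as it is.

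A minimum of 21 would be enough only if the last block is always complete; otherwise it gives 14 on average. Forcing completion would alter a scheme generated before recruitment and make the last assignments in a cohort easier to infer, so 22 is the simpler choice.

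The cost is one number in the text and, for a cohort that would have started at 20 or 21, a wait for one or two more women. That wait still has to fit the four-week baseline window in Table 1.
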